### Participant timeline {13}

Participation burden consists of filling out questionnaires. The first questionnaires (t = 0 pre-operative) are handed out pre-operatively, (DASH, use of analgesics, BreastQ). Patients are asked to notate the VAS daily during the first two weeks postoperative. Two weeks postoperatively, at scheduled postoperative evaluation, participants will be evaluated by physical examination, a picture of the amputated breast will be taken by the treating surgeon or breast cancer nurse, combined with the DASH questionnaire and use of analgesics again (t = 1). Follow-up lasts for 6 months postoperatively when another picture of the amputated breast is taken and the final DASH and analgesic are completed (t = 2). Additionally, the BreastQ mastectomy module is questioned (Table 1).

**Table 1 Tab1:** Participant timeline

	**Enrolment**	**Operation**	**Days 1–14 postoperative**	**2 weeks postoperative**	**6 months postoperative**
Patient information form	X				
Letter of objection	X				
Physical examination				X	X
Picture of the thoracic wall				X	X
Questionnaires - DASH - Use of analgesics - Breast Q	X			X	X
VAS pain scores			X		

### Sample size {14}

To calculate the sample size of a randomized controlled trial TO is assumed to be 30% without quilting, as based upon a pilot study [7]. A doubling of TO is considered clinically significant, resulting in a TO of 60% with quilting. In this study 2 treatment arms will be used, with a significance level of 0.05 and power of 80%. For a parallel randomized trial in which *patients* are randomized, a minimum of 44 patients need to be included:$$2* {\left({\mathrm{Z}}_{\frac{0.05}{2}}+{\mathrm{Z}}_{0.80}\right)}^{2}*\frac{1}{{0.30}^{2}}* 0.45\left(1-0.45\right)=44$$

However, since in the present study *clusters* and not patients are randomized, we need to correct for the fact that outcomes within clusters are very likely more similar than those between clusters. The degree of similarity is estimated using the intra-cluster correlation coefficient (ICC) [35]. This was estimated to be on average 0.028, based upon the pilot study of the 2 hospitals with the variables age, body weight, ASA classification, type of surgery, neo-adjuvant chemotherapy, radiotherapy, tumour classification and first or second episode of breast cancer.

Consequently, the formula as proposed by Hemming et al. was used to correct for this similarity with a total of nine clusters and nine steps [36]. This led to a minimum of 94 patients in total or 11 per centre. A margin safety of 20% was introduced to correct for loss-to-follow-up, which led to a total of 113 patients or 13 per centre. Based on an average of 50 mastectomies each year per centre, the duration of the total inclusion should take 3 months. To correct for the probability of non-adherence to the quilting technique since it is new implemented for all surgeons (safety margin of 20%) each step will take 2 weeks. Suspected transition period and learning curve was suspected to be eight weeks.

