**Methods:**

The QUILT study is a stepped wedge design study performed among nine teaching hospitals in the Netherlands. The study consists of nine steps, with each step one hospital will implement the quilting suture technique. Allocation of the order of implementation will be randomization-based. Primary outcome is ‘textbook outcome’, i.e.no wound complications, no re-admission, re-operation or unscheduled visit to the outpatient clinic and no increased use of postoperative analgesics. A total of 113 patients is required based on a sample size calculation. Secondary outcomes are shoulder function, cosmetic outcome, satisfaction with thoracic wall and health care consumption. Follow-up lasts for 6 months.

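### The sample-size formula gives 44 patients per arm, but 44 is stated as the trial's number; with calendar time in the model, 94 evaluable patients give about 58–62% power, not 80%

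*Protocol article*

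**What the plan says.** Under Sample size {14}, the protocol article sets the control rate of textbook outcome ("TO is assumed to be 30% without quilting") and the target ("resulting in a TO of 60% with quilting"). It describes two arms "with a significance level of 0.05 and power of 80" per cent. It prints 2 × (Z for 0.05/2 + Z for 0.80)² × (1/0.30²) × 0.45 × (1 − 0.45) = 44 and concludes that, with patients randomised individually, "a minimum of 44 patients need to be included". Neither a per-arm label nor a total of 88 appears anywhere.

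The section then allows for clustering. Of the ICC it says "This was estimated to be on average 0.028". A cited formula is applied for nine clusters and nine steps: "This led to a minimum of 94 patients in total or 11 per centre". A 20% margin for loss to follow-up raises this to 113, which the abstract repeats: "A total of 113 patients is required based on a sample size calculation". The number of patients per hospital and period that entered the correction is not given.

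Statistical methods {20a} names a logistic mixed model with a random intercept for cluster. It mentions no term for calendar period.

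**The concern.** The leading 2 in the printed formula is the variance factor for a difference between two equal arms, so the result is the size of each arm. The text treats it as the number to include in the whole two-arm trial. If that number was then scaled to the stepped-wedge total, the target is about half of what the stated power requires.

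The trial's 80% power for its primary endpoint rests on 94 and 113. If true power is nearer 60%, a null result would say little about whether quilting doubles textbook outcome, which is the effect the protocol calls clinically significant.

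**Working it through.** **Inputs from the protocol article.** Rates 0.30 and 0.60 (mean 0.45, difference 0.30); two-sided alpha 0.05; power 0.80; ICC 0.028; 9 clusters; 9 steps; 50 mastectomies a year per centre; two-week steps. **Assumptions.** One baseline period (10 periods in all) unless stated otherwise; equal patient numbers per hospital and period; outcome variance 0.45 × 0.55 = 0.2475; the standard published stepped-wedge design effect, since the cited source is not available.

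**1. The printed formula.** 2 × (1.960 + 0.8416)² × 0.2475 / 0.09 = 43.17, rounded to 44. This reproduces the plan's figure. Power with n per arm is Φ(0.30 / √(2 × 0.2475/n) − 1.96):
- n = 22 (44 in total): 52%
- n = 44 (88 in total): 81%

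So 44 is a per-arm number.

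**2. From 44 to 94.** With k = 9 steps, one baseline period, r = 0.028 and m patients per hospital-period:

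DE = (k + 1) × [1 + r(km + m − 1)] / [1 + r(km/2 + m − 1)] × 3(1 − r) / [2(k − 1/k)]

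| m | Where m comes from | DE | 44 × DE | 88 × DE |
|---|---|---|---|---|
| near 0 | lower limit | 1.640 | 72 | 144 |
| 1.04 | 94 patients / 90 hospital-periods | 1.831 | 81 | 161 |
| 1.92 | 50 a year, two-week periods | 1.954 | 86 | 172 |
| 3.7 | solved to give 94 | 2.136 | 94 | 188 |
| 4.17 | 50 a year, monthly periods | 2.174 | 96 | 191 |

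At m = 4.17 the unrounded base gives 43.17 × 2.174 = 93.8, i.e. 94. No value of m takes 88 to 94. Without a baseline period the factor (k + 1) becomes k, so the lower limit is 88 × 1.640 × 9/10 = 130, still well above 94.

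A second route exists. The ordinary cluster design effect 1 + (m − 1)r at m = 4.17 is 1.0887, and the unrounded two-arm total 86.34 × 1.0887 = 94.0. That correction contains nothing for calendar time.

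**3. Power with period effects.** At N = 94, m = 94/90 = 1.04 and DE = 1.831. The effective size per arm is 94 / (2 × 1.831) = 25.7, so SE = √(2 × 0.2475/25.7) = 0.139 and power = Φ(0.30/0.139 − 1.96) = 58%. Generalised least squares with a random hospital intercept and fixed period effects gives the same SE and 57.9%.

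| Evaluable N | With baseline period | No baseline period |
|---|---|---|
| 94 | 58% | 62% |
| 113 | 65% | 69% |
| 168 | 80% | 83% |

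The difference detectable at 94 with 80% power, with a baseline period, is (1.960 + 0.8416) × 0.139 = 0.39.

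**4. Sensitivity at 94, with a baseline period.** ICC from 0 to 0.2: 54–61%. Unpooled variance (0.225): 62%.

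**5. Model without calendar time.** Random hospital intercept only: 82% at 94.

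**6. Accrual in the planned steps.** 9 centres × 50 × 18/52 = 156, or 173 with one more two-week period. After 20% loss, 125 to 138 remain evaluable, giving 69–73% with a baseline period.

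**The case against.** Four points can be made for the plan.

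*The route to 94 is not shown.* A reader might infer that the plan is proven to have used 44 as the whole trial. It is not. Starting from 44 gives exactly 94 only at about 3.7–4.2 patients per hospital-period, whereas 94 patients spread over 90 hospital-periods is about 1.04, and at that size 44 becomes about 81. The ordinary cluster correction of 86 gives 94 equally well. This stands, so the halved base is likely rather than established. The mention of nine steps and the statement of 44 as the number to include both favour it. The alternative does not rescue the power, because it omits calendar time.

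*The only model named has no period term.* Under it, power at 94 is about 82%, so an unconditional claim of 58% would go too far. This also stands. But in a stepped wedge the share of quilted patients rises with calendar time, so that model attributes any time trend to quilting. A standard stepped-wedge sample-size correction presupposes period effects.

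*The numbers are minimums.* A reader might infer that inclusion stops at 113. The document states no such rule. Steps are defined by time, and Recruitment {15} says missing inclusions are accounted for in step duration. That bears on what the trial may eventually collect, but leaves the stated requirement wrong.

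*Condensed reporting.* An article leaves detail to the full protocol. Here, however, the formula, its result, the wording and the totals are all printed.

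**Conclusion.** The point holds in a qualified form. That 44 is a per-arm figure presented as the trial's number follows from the printed formula alone. The step to 94 most likely inherits this error; the other arithmetic route ignores calendar time. Under either explanation, 94 evaluable patients do not give 80% power in a standard stepped-wedge analysis: power is about 58%, or 62% without a baseline period. At 113 evaluable, that is with no losses at all, it is 65–69%. With a baseline period, about 168 evaluable patients are needed.

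These figures rest on period effects in the model, ICC 0.028, equal cluster-period sizes and use of all periods. The article does not say that patients in the eight-week transition are left out of the analysis; if they were, power would be lower.

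A reader might also infer that the shortfall disappears if every eligible patient in the planned steps is kept, since 156–173 patients would give about 77–81% with a baseline period. That holds only before losses. With the protocol's own 20% loss it is 69–73%, so the 80% claim needs restating in any case.

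**What to change.** In Sample size {14}:

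1. State that 44 is per arm and that an individually randomised trial needs 88 in total.
2. Redo the stepped-wedge correction from 88. Show the formula, the cluster-period size, whether there is a baseline period, and the calendar-time assumption, and make that assumption agree with the model in Statistical methods {20a}.
3. Restate power and detectable difference at 94 and 113 evaluable patients. With a baseline period and period effects these are about 58% and 39 points at 94, and about 65% and 36 points (2.80 × 0.128) at 113. Correct the abstract to match.
4. Optionally, say that all eligible patients accrued over the planned two-week steps will be kept, and quote the resulting 69–73% after 20% loss.

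Items 1 to 3 cost rewording and a less favourable stated power. Item 4 needs no new sites or steps, but it does not restore 80%. Keeping the 80% claim with a baseline period means about 168 evaluable patients, or 168 × 1.2 = 202 recruited on the plan's own margin. That exceeds the 156–173 expected from the planned steps, so it would require more accrual than is now planned.

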### Methods in analysis to handle protocol non-adherence and any statistical methods to handle missing data {20c}

Stochastic regression imputation will be used to impute missing data.

Patients lost to follow up will be excluded from the study.

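### The 20% margin for loss to follow-up is applied as 94 × 1.2 = 113, which protects the stated minimum of 94 only up to 16.8% loss; 20% loss needs 118

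*Protocol article*

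**What the plan says.** The protocol article, Sample size {14}, corrects an individually randomised calculation for clustering, using an intra-cluster correlation of 0.028 and a design "with a total of nine clusters and nine steps". The result is given as follows: "This led to a minimum of 94 patients in total or 11 per centre". The next sentence inflates it: "A margin safety of 20% was introduced to correct for loss-to-follow-up, which led to a total of 113 patients or 13 per centre". The Methods paragraph of the abstract repeats the inflated total as the requirement: "A total of 113 patients is required based on a sample size calculation".

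Section {20c} says what happens to patients who drop out: "Patients lost to follow up will be excluded from the study". The same section plans stochastic regression imputation for missing data.

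No other passage gives an anticipated loss rate. A second 20% margin appears in Sample size {14}, but it is assigned to non-adherence to quilting and is applied through the length of the steps.

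**The concern.** A margin for loss to follow-up should leave the required number of patients once the loss has happened. If a fraction d is lost, a total N leaves N × (1 − d), so N must be n/(1 − d). Adding d to n instead gives n × (1 + d), which is always too small, because (1 + d)(1 − d) = 1 − d² is less than 1.

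The loss comes straight off the analysed number here. Excluded patients gain nothing from the planned imputation. The primary endpoint, textbook outcome, is measured at 6 months and includes analgesic use at that time (Outcomes {12}), so patients who leave before 6 months are the ones affected.

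At stake is whether the total published as required delivers the minimum that the plan sets for 80% power.

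**Working it through.** **Inputs**, all from Sample size {14} unless noted:
- minimum before loss: n = 94 (11 per centre)
- margin for loss: d = 0.20
- stated total: 113 (13 per centre), nine centres
- two-sided significance level 0.05, power 80%
- average of 50 mastectomies per centre per year
- nine steps of two weeks (also Study setting {9})
- lost patients excluded (section {20c})

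**1. The plan's own figure**

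n × (1 + d) = 94 × 1.20 = 112.8, rounded up to 113. This matches exactly, so the rule used is clear. Per centre, 113/9 = 12.6, rounded up to 13.

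**2. What 113 leaves after 20% loss**

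113 × 0.80 = 90.4, so about 90, roughly 4 below the minimum of 94.

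**3. The loss that 113 does cover**

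1 − 94/113 = 0.168, so 16.8%.

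**4. The total that covers 20% loss**

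n/(1 − d) = 94/0.80 = 117.5, rounded up to 118. Check: 118 × 0.80 = 94.4, which meets 94. The difference from the stated total is 118 − 113 = 5 patients. Per centre, 118/9 = 13.1; rounding up to 14 gives 9 × 14 = 126 in all, so 14 per centre overshoots 118 purely through rounding.

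**5. The per-centre target in the same sentence**

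9 × 13 = 117, and 117 × 0.80 = 93.6. If every centre reaches 13, the gap to 94 is less than one patient.

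**6. Power**

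Take 94 as giving exactly 80% power, and let the test statistic scale with the square root of the number analysed (normal approximation, clustering ignored):

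(1.960 + 0.842) × √(90.4/94) − 1.960 = 2.802 × 0.9807 − 1.960 ≈ 0.787

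The normal probability below 0.787 is about 0.785, so power is about 78.5%, a loss of about 1.5 points.

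**7. Accrual by time**

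9 × 50 = 450 mastectomies per year. Nine two-week steps last 18 weeks: 450/52 × 18 = 155.8, about 156 patients. With 20% lost, 156 × 0.80 ≈ 125 remain. With a further 20% removed for non-adherence, 156 × 0.80 × 0.80 ≈ 100 remain. Both exceed 94. This assumes that every mastectomy is eligible and included, and that patients operated on during the 8-week transition period count; the article does not say that they are dropped.

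**The case against.** **The text names a margin, not an expected loss.** Read literally, 20% on top of 94 is 113, and the multiplication is right. This stands as a possible reading, so the sentence is not simply a slip of arithmetic. But the sentence gives the purpose of the margin as correcting for loss to follow-up, and no other loss rate appears. Someone planning or monitoring the trial would take 113 as safe against 20% loss. On the literal reading it is safe only up to 16.8%, and the article does not say so.

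**The per-centre figure nearly closes the gap.** This stands too. Thirteen per centre is 117, one short of 118. The two figures in the sentence differ by rounding, and the smaller one is what the abstract reports as required.

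**Recruitment is set by time.** A reader might infer from the 90 evaluable patients that the trial will fall short of its minimum. The documents do not support that. Nothing makes 113 a cap, Recruitment {15} says that missed inclusions are allowed for in the duration of the steps, and the stated rate over 18 weeks gives about 156 patients. Against this, Sample size {14} also puts total inclusion at 3 months, and 450/4 = 112.5 suggests that this period was matched to 113. So accrual may exceed 118, but that is neither assured nor a reason to leave the requirement misstated.

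**The base of 94 may itself need revisiting.** It is taken as given here. It could not be reproduced exactly, because the number of patients per centre and period is not stated. If it changes, 118 changes with it, but the inflation rule still needs correcting.

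**Conclusion.** The point holds as a small error in a stated figure. If the margin means 20% loss, the required total should be 118, not 113, and 113 would leave about 90 evaluable patients against a minimum of 94. If it means 20% on top, 113 is correctly multiplied but covers 16.8% loss, which the article does not state. Either way, the abstract and the sample size section need a correction or a clarifying phrase.

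The size is 5 patients and about 1.5 points of power, on the assumptions that 94 gives 80% power, that lost patients are excluded as planned and that clustering can be ignored for this comparison. No analysis or endpoint is affected, and an actual shortfall at the end of the trial is not shown.

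**What to change.** In Sample size {14} and in the Methods paragraph of the abstract, do one of two things:
- restate the required total as 118 for 20% loss to follow-up, noting that 14 per centre is a rounding up that gives 126 in all; or
- keep 113 and state that it preserves 94 evaluable patients for loss of up to 16.8%.

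If the base of 94 is recalculated, apply n/(1 − loss) to the new figure.

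The cost is one figure or one phrase in two places, with no change to design or analysis. Under the first option the requirement rises by five patients, which is within the accrual that the stated rate implies over nine two-week steps.

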### Recruitment {15}

Each hospital assigns a local investigator. The lead investigator maintains contact once every two weeks with each local investigator and monitors recruitment and progress in Castor electronic data capture system (https://www.castoredc.com). Each local investigator monitors local inclusions to make sure all patient receive a patients information and objection form prior to surgery. Furthermore ‘missing inclusions’ are accounted for in the duration of each step and thus the duration of the study (sample size).

### Assignment of interventions: allocation

#### Sequence generation {16a}

At the beginning of the study all hospitals will be randomly assigned to a step. Randomization will be performed with an online randomisation tool by the lead investigator at the beginning of the study.

### Concealment mechanism {16b}

Not applicable.

### Implementation {16c}

Before the start of the study, the lead investigator visits each hospital to inform the professionals involved with breast cancer at the outpatient clinic of the department of surgery of participating hospitals. Implementation of quilting is monitored in each hospital, after randomisation quilting becomes standard practice and all patients undergoing mastectomy and/or axillary lymph node dissection will be quilted, including those individuals who decide not to participate in the study. The quilting technique is a straightforward technique and will be demonstrated and instructed to surgeons by video instructions. On request, surgeons are welcome to join a quilting procedure at the Canisius Wilhelmina Hospital and on site teaching can be provided by an experienced breast surgeon.

### Assignment of interventions: Blinding

#### Who will be blinded {17a}

Not applicable, no blinding.

### Procedure for unblinding if needed {17b}

Not applicable.

### Data collection and management

#### Plans for assessment and collection of outcomes {18a}

Outcome variables are extracted from the electronic patient file by the local investigator.

Baseline characteristics and variables of health care consumption will be collected by data managers.

Data collection forms are constructed in Castor, questionnaires will also be registered in Castor, questionnaires can be sent digital from Castor depending on patients preference.

#### Questionnaires

- DASH [33]- BreastQ [34, 37].

Pictures of the breast will be taken by the treating surgeon or breast cancer nurse in a standardized fashion. Pictures will be collected by the lead investigator. A panel of four experienced breast surgeons will blindly assess the pictures.

### Plans to promote participant retention and complete follow-up {18b}

The return of questionnaires is monitored by the local and the lead investigator. Participants are contacted by telephone by the local investigator in case of missing questionnaires. Questionnaires can be provided on the outpatient clinic, send digital by mail or a hard copy can be sent by post. Patients will also be contacted by phone if the returned questionnaire does not meet the requirements of assessment.

### Data management {19}

Collected data from the electronic patients files and received questionnaires are processed (coded) into Castor by the local investigator. The key (patient identification list) to the coded data remains safely (locked) in each local hospital and is only accessible for the local investigator. Data extracted from Castor is anonymous and will be handled confidentially and stored not identifiable at the Canisius Wilhelmina Hospital. The collected information will be stored safely for 15 years. The handling of personal data complies with the EU General Data Protection Regulation and the Dutch Act on implementation of the General Data Protection Regulation (in Dutch: Uitvoeringswet AVG, UAVG). The datasets used and/or analysed during the current study are available from the authors on reasonable request.

### Confidentiality {27}

Objected consent forms and collected questionnaires contain personal information. In order to protect confidentiality before, during and after the study these collected papers will be stored safely in an file in a locked room in each local hospital for 15 years.

### Plans for collection, laboratory evaluation and storage of biological specimens for genetic or molecular analysis in this trial/future use {33}

Not applicable.

### Statistical methods

#### Statistical methods for primary and secondary outcomes {20a}

Primary outcome is a binary outcome presented as number of cases and percentage. Nominal data will also be presented as percentage. Continuous data will be presented as mean ± standard deviation or median ± interquartile range, based upon whether the assumption of normality holds (visual interpretation). Analysis of continuous data will be performed by applying the Students T-test for unpaired data in case of continuous variables with a normal distribution. Otherwise the distribution will be compared using the Mann–Whitney U-test. Chi2 test will be used for comparisons of categorical variables between the two groups. The Fisher’s exact test will be performed where applicable. Since data is clustered analysis will be performed using a generalized logistic mixed-effects model with cluster as random intercept. A P-value < 0.05 is considered statistically significant.

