### Study design {8}

The QUILT study is a stepped wedge cluster randomized study.

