## Methods: Participants, interventions and outcomes

### Study setting {9}

The organizing hospital, Canisius Wilhelmina Hospital, is excluded from participation because the quilting suture technique already is standard care for multiple years. The participating nine hospitals provide standard care by conventional wound closure with postoperative drainage. These nine hospitals will be randomized for implementation of the quilting suture technique as a cluster. With each step every two weeks, one cluster is randomised to implement the quilting suture technique, there will be nine steps. Transition period or learning curve is expected to be 8 weeks. Follow up continues for six months postoperatively (Fig. 1). At T1 all hospitals start including patients.

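### The tests fixed for continuous secondary outcomes have no hospital or calendar-time term, so in this stepped wedge any drift over time enters the quilting effect

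*Protocol article*

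**What the plan says.** Study design {8} states: "The QUILT study is a stepped wedge cluster randomized study". Study setting {9} gives the roll-out: "With each step every two weeks, one cluster is randomised to implement the quilting suture technique, there will be nine steps". It adds: "Transition period or learning curve is expected to be 8 weeks". Sample size {14} accepts that "outcomes within clusters are very likely more similar than those between clusters" and uses an ICC of 0.028, the only one in the document.

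Statistical methods {20a} then fixes the tests. For normally distributed outcomes: "Analysis of continuous data will be performed by applying the Students T-test for unpaired data". For the rest: "Otherwise the distribution will be compared using the" Mann-Whitney U-test. Chi-square or Fisher tests are set for categorical data. One sentence on clustering follows: "Since data is clustered analysis will be performed using a generalized logistic mixed-effects model with cluster as random intercept". No calendar-time or period term appears anywhere in the section.

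Two related statements bear on the fix. Under Participant timeline {13}, the first questionnaires "are handed out pre-operatively, (DASH, use of analgesics, BreastQ"), so DASH and BreastQ have pre-operative values. Secondary study parameters/endpoints lists re-admission and re-operation with the median as their summary, and codes day care as 0 for hospital stay.

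**The concern.** Both named tests treat patients as independent and exchangeable over time. Here they are neither. Patients are grouped in nine hospitals, and every hospital moves in the same direction, from conventional closure to quilting. Condition is therefore tied to calendar time by design. Randomising the order of hospitals does not break that tie; a period term in the analysis does.

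The sentence on the mixed model does not repair this. A logistic model, as named, fits binary outcomes and not DASH scores, minutes of surgery or nights in hospital. Read generously as a mixed model of any kind, it still has no time term, and it then conflicts with the t-test sentence.

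The Introduction gives pain, shoulder function, cosmetic result and operating time as the reasons why surgeons hesitate. Most of these are continuous outcomes, so a contrast mixed with time could create or hide a harm on the points the trial is meant to settle.

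**Working it through.** **Inputs from the protocol article.** Nine hospitals, nine steps and two-week periods (Study setting {9}); 8-week transition, that is four periods (same section); ICC 0.028, 94 patients before and 113 after the loss margin (Sample size {14}). The 113 reproduces as 94 × 1.2 = 112.8. No power or precision is stated for continuous outcomes, so there is no such figure to reproduce.

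**Assumptions.** One all-control period before the first step; equal cell sizes; outcome in SD units; linear drift from first to last period. Layout A has 10 periods and no transition excluded. Layout B has 14 periods with each hospital's four transition periods excluded. The stepped wedge figure is not shown, so both layouts are assumed. Each has 45 control and 45 quilting cells.

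**Step 1: how much later quilted patients are operated on.**
- Layout A: mean period 7.33 for quilting and 3.67 for control; (7.33 − 3.67)/9 = 0.41 of the wedge.
- Layout B: (11.33 − 3.67)/13 = 0.59.

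The bias of the two-group contrast is this fraction times the drift.

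**Step 2: ignoring hospital, no drift.** The t-test assumes variance 2/56.5 = 0.0354 (SE 0.188). The true variance is (1 − ICC) × 0.0354 + ICC × 0.1185. Here 0.1185 = Σ(10 − 2k)²/45² over k = 1 to 9, the squared imbalance between conditions within hospitals.

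| ICC | variance ratio | SE ratio | type I error, t cut-off | type I error, 1.96 cut-off |
|---|---|---|---|---|
| 0.028 | 1.066 | 1.03 | 5.5% | 5.8% |
| 0.10 (assumed) | 1.235 | 1.11 | 7.5% | 7.8% |
| 0.20 (assumed) | 1.470 | 1.21 | 10.2% | 10.6% |

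With 94 patients analysed, the t cut-off gives 5.3%, 6.7% and 8.8%.

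**Step 3: adding drift, ICC 0.028, 113 patients.** Type I error = 1 − Φ((c − b)/s) + Φ((−c − b)/s), with c = 1.98 × 0.188 = 0.373, s = √0.0377 = 0.194 and b the bias from Step 1.

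| assumed drift | bias, layout A | type I error, A | bias, layout B | type I error, B |
|---|---|---|---|---|
| 0.25 SD | 0.10 SD | 8.9% | 0.15 SD | 12.7% |
| 0.5 SD | 0.20 SD | 19% | 0.30 SD | 34% |
| 1.0 SD | 0.41 SD | 57% | 0.59 SD | 87% |

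The Mann-Whitney test was not computed; it ignores the same structure.

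**Step 4: standard error with hospital and period in the model.** Generalised least squares with a hospital random intercept and period fixed effects gives 0.257 SD in layout A (0.257/0.188 ≈ 1.36) and 0.459 SD in layout B (0.459/0.188 ≈ 2.4).

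**Step 5: the pre-operative score.** Adjustment multiplies the SE by about √(1 − r²): 0.95, 0.87 and 0.71 at assumed correlations of 0.3, 0.5 and 0.7. It can apply only to DASH and BreastQ; VAS, operating time and hospital stay have no pre-operative value.

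**Step 6: medians.** If fewer than half the patients have an event, the median is 0. At an assumed 20% event rate, the chance of a median above 0 in 56 patients is about 1 in 10 million.

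**The case against.** The strongest objection is that these are secondary outcomes, that an analysis plan may exist, and that the section does acknowledge clustering. The first part stands and limits the weight of the point. The other two do not remove it: the protocol is not silent but names the tests, and the clustered model it names does not fit these outcomes.

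Four stronger readings are tempting and should not be made.

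- A reader might infer that the standard errors are badly wrong because hospital is ignored. At the protocol's only ICC the true SE is 1.03 times the naive one. Larger errors need ICCs of 0.10 to 0.20, which are assumptions.
- A reader might infer that the effects are known to be confounded, for example that operating time and stay vary strongly between hospitals or drift with the move to day care. The documents give no ICC for these outcomes and no trend. The Introduction and Discussion present day care as an expected result of quilting without drains, not as a separate calendar trend. Nine two-week steps span only 18 weeks, so drift may be small.
- A reader might infer that leaving out the baseline scores biases the result. It mainly costs precision, and covariates are commonly left to an analysis plan.
- A reader might infer that re-admission and re-operation are lost from view. Both are components of textbook outcome, and the Cost analysis section counts them; only the stated summary is uninformative.

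**Conclusion.** The point holds for the continuous secondary outcomes: the text fixes tests that are open to calendar-time confounding, and it names no usable clustered model for them. Time is the main problem. The contrast takes in 0.41 to 0.59 of whatever drift exists, depending on how the transition is handled. The resulting error rates depend wholly on a drift that the documents do not give, so they show exposure and do not predict what will happen. Ignoring hospital is minor at ICC 0.028. All figures rest on equal cells, one all-control period, linear drift and a normal approximation. The change should be made, but this is not a fault in the primary result. The logistic model named also lacks a period term; that is a separate matter for the primary outcome.

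**What to change.** - Replace the t-test and Mann-Whitney sentences, as far as they concern treatment effects, with a linear mixed model (or a suitable generalised or ordinal one). Include a hospital random intercept, period effects, a quilting indicator and a small-sample correction for nine clusters.
- Add the pre-operative score for DASH and BreastQ, as a gain in precision.
- For hospital stay use a model that allows zeros. A log transform is undefined for day care coded as 0.
- State whether patients operated on during the 8-week transition enter these analyses, since the bias and the standard error both depend on it.
- Report re-admission and re-operation as number and proportion.

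This needs new wording and more programming, on data already planned. The real price is precision: under the assumed layouts the standard error is about 1.36 times the naive one, or about 2.4 times with the transition excluded. Confidence intervals for shoulder function, pain and operating time will be wider, and the report should say so. For DASH and BreastQ the baseline score recovers part of this.
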